#### Exploratory Outcomes

We examine the possible effects of alcohol and substance use by means of the World Health Organization’s alcohol, smoking, and substance involvement screening test [51]; the alcohol use disorders identification test [52]; and the MINI [30], and we examine demographic factors as moderators to the effects of the nurse-delivered CBT intervention. For these analyses, we fit interaction terms to the models. We also separately assess effects of the treatment in subgroups defined by these factors. If results indicate that the intervention significantly increases adherence, we then assess the extent to which this effect operates through possible mediators (eg, depression, coping, and social support). In the first set of models, we add the main effects of alcohol (as an example) and time (ie, the different assessment time points), in addition to an intervention by alcohol use interaction and intervention by time interaction. We conduct a product of coefficients test for the effect of each mediator as an intervening variable [53]. Statistical significance of the mediated effect will be determined by the asymmetric distribution of products test. This test is conducted separately for the other mediators.

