## Methods

### Trial Design

Project Ziphamandla (meaning *to be empowered* in isiXhosa) is a 2-arm, randomized controlled trial comparing CBT-AD with ETAU among PLWH who are failing, or have failed, first-line ART (see Consolidated Standards of Reporting Trials diagram in Figure 1).

Before randomization to treatment condition, participants complete a diagnostic assessment, clinician-rated measures of depression, and a self-report psychosocial assessment battery. We aim to randomize 160 participants to either CBT-AD (8 sessions) or ETAU. For participants in both conditions, treatment providers receive letters summarizing the results of the participants’ diagnostic assessments. At this point, their treatment providers may further diagnose or treat (with antidepressants) MDD in the participants. Randomization follows approximately 1 month after the baseline assessment, so that stratification can occur by those who may or may not have commenced antidepressants as part of their care, following this letter. The 1-month period from baseline to randomization also allows for a baseline assessment of ART adherence using Wisepill real-time electronic adherence monitoring. For participants in both arms, there are 4 major study assessment points: baseline, post intervention (4-month), 8-month, and 12-month.

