##### Assessment of Adherence to Antiretroviral Therapy

Wisepill is a real-time, electronic adherence monitoring system that comprises a pillbox container fitted with a global system for mobile communication chip. Using mobile phone technology, the Wisepill transmits a real-time signal to the Wisepill Web server each time the pillbox is opened. The Wisepill Web server can be securely accessed from any computer via the Wisepill Technologies website with the use of a designated log-in and password. It captures real-time data on device openings and, hence, provides the results of weekly assessments for longitudinal modeling. For the purposes of this study, we did not establish a *window* for missed doses; they were just counted as whether or not they opened the device the required number of times (ie, if they opened the device on 2 separate occasions for a twice daily regimen, it would be counted as fully adherent for the day, and if they opened it once for a twice daily regimen, it would be counted as 50% for the day). To ensure the Wisepill device is working properly, we check in with participants at approximately half-way between major study visits (ie, at approximately 2, 6, and 10 months in study participation). In addition, we monitor Wisepill functionality between the baseline visit (when the device is issued) and the randomization visit. To ensure the device is working properly, if no signal is detected from the Wisepill device for 3 or more days in a row within the first week after the device has been issued, we contact the participant to ascertain if they are experiencing any issues with their device. The purpose of these check-ins is solely to enquire about any difficulties using the Wisepill device. The Wisepill Web server also monitors device battery levels, and participants whose devices had low battery are contacted to remind them to charge the Wisepill device.

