#### Secondary Outcome Measures

Secondary outcome measures include viral load, analyzed categorically (suppressed vs not) at the 12-month outcome, using <400 copies/mL as suppressed (consistent with recent work analyzing chart-extracted viral load data from the same clinics in Khayelitsha). CD4 is analyzed continuously at the 12-month outcome. In addition, HIV medication adherence and depression scores over time are examined as secondary outcomes using the 4-, 8-, and 12-month assessment time points.

The ultimate data analytic approach will depend on the distribution of the data. We anticipate that we will use generalized linear models), which are estimated using generalized estimating equations with robust standard error estimates to account for repeated measures of the outcome. For the primary outcomes, we will examine adherence scores longitudinally using the Wisepill data and Hamilton scores using the 2 time points (baseline to 4 months) comparing the 2 study arms. For outcomes assessed at the 4 major assessments (ie, baseline and 4, 8, and 12 months), we will use repeated measures analyses. For 12-month viral load, we will test the proportion of those who are suppressed using Fisher exact test. If continuous viral load data are analyzed, we will make log transformations and examine viral load using repeated measures. To reduce bias, the intention-to-treat principle is utilized, where individuals are analyzed according to the condition they were randomized, regardless of their fidelity to that condition.

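### The exploratory moderator model has no intervention-by-moderator-by-time term, so wherever baseline is an outcome row its intervention-by-alcohol coefficient under-estimates moderation (by 25% with four rows, 50% with two, if moderation is constant after baseline)

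*Protocol article*

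**What the plan says.** All references are to the protocol article.

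- **Exploratory Outcomes** gives the terms of the moderator model. The lower-order terms are one for the moderator, with alcohol as the worked example, and one for assessment time. These enter "in addition to an intervention by alcohol use interaction and intervention by time interaction". The section names neither a three-way term nor an alcohol-by-time term, and it does not say whether baseline is one of the outcome rows. It also plans separate treatment effects within subgroups.
- **Trial Design** counts baseline as an assessment point: "there are 4 major study assessment points: baseline, post intervention (4-month), 8-month, and 12-month".
- **Secondary Outcome Measures** describes the outcome models in three ways:
  - The primary depression analysis takes "Hamilton scores using the 2 time points (baseline to 4 months) comparing the 2 study arms".
  - More generally, "For outcomes assessed at the 4 major assessments (ie, baseline and 4, 8, and 12 months), we will use repeated measures analyses".
  - For the longitudinal secondary outcomes, however, "depression scores over time are examined as secondary outcomes using the 4-, 8-, and 12-month assessment time points", without baseline.
- **Assessment of Adherence to Antiretroviral Therapy** says that the Wisepill device "provides the results of weekly assessments for longitudinal modeling", so adherence has many more rows than two or four.

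**The concern.** When baseline is an outcome row, the arms are alike there in expectation and separate only afterwards. The treatment effect is therefore the intervention-by-time term. A moderator changes that effect, so moderation is intervention by moderator by time. The listed intervention-by-alcohol term is constant over time. It estimates one average over all rows, including a row collected before anyone was treated.

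Two things follow. A real moderator is estimated as weaker than it is, usually with less power to detect it. The two planned moderator analyses also stop matching: with baseline as a row, each subgroup effect is an intervention-by-time effect, and the difference between two subgroups is the three-way term. The listed interaction does not test that difference.

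**Working it through.** The article gives no figure for the moderator analysis, so there is nothing to reproduce first.

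**Inputs from the article.** Model terms (Exploratory Outcomes); rows at 0 and 4 months, at 0, 4, 8 and 12 months, or at 4, 8 and 12 months (Secondary Outcome Measures); a baseline adherence period of about one month, taken as 4 weekly rows (Trial Design); within-subject correlation 0.5 and type I error 5% (Sample Size Considerations).

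**Assumptions.** Two-sided test, balanced arm-by-alcohol cells, complete data, a moderator that does not change over time, exchangeable correlation, and true moderation of zero at baseline.

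**Step 1: what the listed coefficient estimates.** In balanced complete data the intervention-by-alcohol column is constant within a participant and orthogonal to the time terms. Its coefficient is therefore the plain mean of the row-by-row moderation. With moderation 0 at baseline and 1 at each of k follow-up rows, the share recovered is k/(k + number of baseline rows).

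| Outcome rows | Share recovered | Loss |
|---|---|---|
| 0, 4 months | 1/2 = 0.50 | 50% |
| 0, 4, 8, 12 months | 3/4 = 0.75 | 25% |
| 4, 8, 12 months only | 3/3 = 1.00 | none |
| Weekly, 4 baseline + 13 later (assumed) | 13/17 = 0.76 | 24% |
| Weekly, 4 + 17 (assumed) | 17/21 = 0.81 | 19% |
| Weekly, 4 + 48 (assumed) | 48/52 = 0.92 | 8% |
| Weekly, 4 + 52 (assumed) | 52/56 = 0.93 | 7% |

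An exact generalized least squares calculation gave the same shares for the visit-based rows at correlations 0, 0.5 and 0.8, with time categorical or linear.

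**Step 2: other time courses, four rows.**
- Moderation at month 4 only: (0 + 1 + 0 + 0)/4 = 0.25 of the month-4 value.
- Linear growth to month 12: (0 + 1/3 + 2/3 + 1)/4 = 0.50 of the month-12 value.
- Fading 1, 0.5, 0.25: 1.75/4 = 0.44 of the month-4 value.

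Not all of this loss comes from baseline. A constant interaction fitted to the three follow-up rows would itself give 1/3, 2/3 and 0.58. The baseline row multiplies each of these by 3/4.

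**Step 3: signal-to-noise.** With k follow-up rows, T = k + 1 and correlation ρ, for unit moderation and up to a common factor:
- listed term: (k/T)/√[(1 + (T−1)ρ)/T]
- three-way term (post-baseline mean minus baseline): 1/√[(1−ρ)(1 + 1/k)]
- follow-up rows adjusted for baseline: 1/√[(1 + (k−1)ρ)/k − ρ²]

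At ρ = 0.5:

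| | Listed | Three-way | Baseline-adjusted |
|---|---|---|---|
| k = 3 | 0.75/√0.625 = 0.949 | 1/√0.667 = 1.225 | 1/√0.417 = 1.549 |
| k = 1 | 0.50/√0.75 = 0.577 | 1/√1 = 1.000 | 1/√0.75 = 1.155 |

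**Step 4: power.** A two-sided 5% test with 80% power has noncentrality 1.96 + 0.84 = 2.80.
- Four rows, three-way at 80%: 2.80 × 0.949/1.225 = 2.17, and Φ(2.17 − 1.96) ≈ 58% for the listed term.
- Four rows, baseline-adjusted at 80%: 2.80 × 0.949/1.549 = 1.72, and Φ(1.72 − 1.96) ≈ 40%.
- Two rows, baseline-adjusted at 80%: 2.80 × 0.577/1.155 = 1.40, and Φ(1.40 − 1.96) ≈ 29%.

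**Step 5: sensitivity to the correlation.** With four rows the ratio of listed to three-way signal-to-noise is 1.088/1.035 = 1.05 at ρ = 0.3 and 0.852/1.581 = 0.54 at ρ = 0.7. At low correlation the listed term loses no power against the three-way term, although its estimate is still 25% too small.

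**The case against.** **The article does not say that baseline is a row of the moderator model.** This stands. The time variable is defined only as "time (ie, the different assessment time points"), and one sentence in Secondary Outcome Measures names follow-up visits alone. On that reading constant moderation is not diluted. The other statements, including the primary comparison of change from baseline in Primary Outcome Measures, do use baseline as a row. The criticism therefore applies to those models and must be conditional.

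**The term list is incomplete, so an unlisted three-way term need not be excluded.** The intervention main effect is not named either, alcohol is only an example, and the analytic approach is described as anticipated. This carries limited weight. A main effect is implied by the interactions built on it, whereas a three-way term is implied by nothing listed. The article chose to state the interactions, so this is more than detail left to a fuller document.

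**Stronger conclusions that a reader might infer.**
- *Any true moderation is diluted by a quarter to a half.* This is not supported: the loss runs from 0 to 75%, depending on the rows, the time course and the visit taken as the target.
- *Chance baseline imbalance will produce false moderators.* This is not supported: without true moderation the coefficient is zero in expectation, and baseline variation is part of its standard error. It adds noise but does not inflate the type I error.
- *The subgroup conclusions rest on this coefficient.* This is not supported: the separate subgroup effects are estimated without it.
- *A real moderator would usually be missed.* The 40% and 29% figures use a baseline-adjusted benchmark, and part of that gap is the efficiency of covariate adjustment rather than the missing term. The article claims no power for moderation.

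**Conclusion.** The point holds in conditional form. If the moderator model is fitted as listed with baseline among the outcome rows, the intervention-by-alcohol coefficient is not the moderation of the treatment effect. For moderation constant after baseline it is 25% too small with four rows and 50% too small with two. For weekly adherence data the loss is about 7-24% under assumed row counts, and with only the 4-, 8- and 12-month rows there is none.

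At the article's correlation of 0.5 with four rows, 80% power for the three-way term corresponds to about 58% for the listed term. That comparison depends on the correlation; the attenuation does not. All figures rest on balanced cells, complete data and a time-invariant moderator. Only the exploratory moderator results are affected, not the primary or secondary treatment comparisons.

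**What to change.** State which outcome rows enter the moderator model, then specify one of two versions:

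1. Fit the follow-up rows only, with the baseline value of the outcome as a covariate, and test intervention by moderator. At correlation 0.5 this has the highest signal-to-noise of the three models above.
2. Keep baseline as an outcome row, add moderator by time and intervention by moderator by time, and test the three-way term as post-baseline versus baseline.

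In either version, take that interaction test as the evidence of moderation, and report the separate subgroup estimates as description rather than comparing their P values. The cost is one line of model specification and, for the second version, a few extra parameters. No new data are needed.

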#### Sample Size Considerations

The study is powered to detect differences in the depression outcome as well as virologic suppression, and accordingly, a sample size of 160 randomized participants is appropriate. Using repeated measurements with a medium effect, we will have almost 90% power to detect a 10% difference in depression with complete retention at randomization, and assuming 20% attrition, we will have 84% power to detect a difference. On the basis of our earlier efficacy trial that was completed when this study was being designed, for those who entered the study with detectable viral load (in this study, all participants entering will have detectable virus), there was a 20% difference in the proportion of those who had undetectable virus at 12-month follow-up: 40% of those in the control condition compared with 60% of those in the experimental condition [27]. On the basis of these effect sizes, for this study, with a sample size of 160, we are powered to detect differences in the secondary binary outcome, virologic suppression, as follows: we will have >90% power to detect at least a 25% difference and >80% power to detect at least a 20% difference in the proportion of those with detectable viral load. These calculations assume a 20% attrition rate that occurs during the active treatment phase of the study, that the proportion of subjects with viral suppression in the usual care comparison condition is 0.4, that the type I error rate is 5%, and that the correlation between observations on the same subject is 0.5.

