#### Secondary Outcomes: HIV Viral Load and CD4 Cell Count

Absolute CD4 cell count and number of HIV viral copies per milli liter of blood are extracted from the participants’ medical record at baseline (to assess the first-line treatment failure inclusion criteria) and at 12-month follow-up. This allows for a calculation of the proportion of patients with virologic suppression. Participants who do not have viral load test results within 1 month of the baseline assessment or 4-, 8-, and 12-month follow-up undergo a blood draw for assay using the COBAS AmpliPrep/TaqMan HIV-1 test (range: 20-10,000,000 copies/mL) [50].

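### The power stated for virologic suppression (>80% for 20 points, >90% for 25 points) does not belong to the planned 12-month Fisher exact test, which has about 54% and 76%

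*Protocol article*

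**What the plan says.** All references are to the protocol article.

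- **Power.** Sample Size Considerations justify 160 participants by the depression outcome and by viral suppression. On the latter: "with a sample size of 160, we are powered to detect differences in the secondary binary outcome, virologic suppression", and then "we will have >90% power to detect at least a 25% difference and >80% power to detect at least a 20% difference".
- **Inputs.** The same section gives the attrition ("These calculations assume a 20% attrition rate that occurs during the active treatment phase of the study"), the control rate ("the proportion of subjects with viral suppression in the usual care comparison condition is 0.4"), a 5% type I error, and "that the correlation between observations on the same subject is 0.5". The 20-point effect is taken from an earlier efficacy trial, where 40% of controls and 60% of the experimental arm had undetectable virus at 12 months.
- **Test.** Secondary Outcome Measures define the outcome as suppressed or not at 12 months, with a threshold of 400 copies/mL, and add: "For 12-month viral load, we will test the proportion of those who are suppressed using Fisher exact test".
- **Repeated measures.** The same section plans repeated-measures analyses for outcomes taken at all four major assessments. For viral load in particular it mentions them only if continuous values are analysed.
- **Data.** Participants without a recent result at baseline or "4-, 8-, and 12-month follow-up undergo a blood draw for assay", so suppression status should exist at each follow-up visit.

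**The concern.** A within-subject correlation matters only when several observations per person enter one analysis. A Fisher test at 12 months uses one. Its presence among the inputs suggests that the power may have been worked out for something other than the named test. It is then natural to ask whether the named test delivers the stated power with 64 per arm.

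The stakes are interpretive. Suppression is a secondary outcome, but it is the only biological outcome with a stated power, and the article uses it to support the sample size. A reader told that power exceeds 80% for a 20-point gain would treat a non-significant 12-month result as fair evidence against such a gain. If the true power is near 54%, that conclusion is not warranted.

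**Working it through.** **Inputs.** 160 randomized in two arms ("We aim to randomize 160 participants to either CBT-AD (8 sessions) or ETAU"); 20% attrition; control suppression 0.40; differences of 0.20 and 0.25; 5% type I error; correlation 0.5. *Assumed, because not stated:* 1:1 allocation, equal attrition in both arms, and a two-sided test. Analysed per arm: 80 × 0.8 = 64.

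**Step 1. Can the stated figures be reproduced?** Try a time-averaged comparison over m visits. The variance factor is (1 + (m − 1)ρ)/m. With m = 3 (4, 8 and 12 months) and ρ = 0.5 it is 2/3, so the effective number per arm is 64 ÷ (2/3) = 96.

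Unpooled normal approximation, power = Φ(difference/SE − 1.96):
- 0.40 vs 0.60: SE = √[(0.24 + 0.24)/96] = 0.0707; 0.20/0.0707 = 2.828; Φ(0.868) = 80.7%.
- 0.40 vs 0.65: SE = √[(0.24 + 0.2275)/96] = 0.0698; 0.25/0.0698 = 3.582; Φ(1.622) = 94.8%.

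| Visits averaged | 20 points (pooled / unpooled variance) | 25 points (pooled / unpooled variance) |
|---|---|---|
| 2 | 74.7% / 76.0% | 91.2% / 92.2% |
| 3 | 79.6% / 80.7% | 94.0% / 94.8% |
| 4 | 82.1% / 83.2% | 95.3% / 95.9% |

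Three visits come close to the stated pair, though the pooled form falls just short of 80%. Four would require counting baseline, which carries no information on suppression because everyone enters with detectable virus.

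**Step 2. Power of the planned test.** For Fisher's exact test, sum the product of the two binomial probabilities over every 2×2 table with p ≤ 0.05:

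power = Σ Bin(x; n, 0.40) · Bin(y; n, p₂) · 1{Fisher p(x, y) ≤ 0.05}

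| Single time point | 0.40 vs 0.60 | 0.40 vs 0.65 |
|---|---|---|
| Stated | >80% | >90% |
| Fisher, two-sided, 64 per arm | 53.9% | 75.6% |
| Fisher, one-sided, 64 per arm | 66.3% | 84.3% |
| Fisher, two-sided, 80 per arm (no attrition) | 65.8% | 85.6% |
| Fisher, one-sided, 80 per arm | 76.7% | 91.7% |
| z-test (pooled), two-sided, 64 per arm | 62.1% | 81.6% |

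Fisher's test misses the 20-point figure in every row. It passes the 25-point figure only if it is one-sided and attrition is ignored. The z-test row shows that the conservatism of Fisher's test explains only part of the gap.

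**Step 3. What the planned test can detect.** With 64 per arm, two-sided, power is 79.3% at 26 points and 82.7% at 27. For 80% power at 20 points it needs 102 analysed per arm (102/0.8 = 127.5, so 128 per arm, 256 randomized). For 90% power at 25 points it needs 87 (87/0.8 = 108.75, so 109 per arm, 218 randomized).

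**The case against.** The strongest reply is that the plan is not confined to Fisher's test. It anticipates generalized linear models fitted by generalized estimating equations, promises repeated-measures analyses for outcomes taken at the four assessments, collects viral load at each of them, and says that the final approach will depend on the data. On that reading a repeated-measures model of suppression is available and the stated power could belong to it.

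Part of this stands. It would go too far to say that the plan contains no analysis to which the figures could apply. But the sentence on 12-month suppression is specific and names Fisher's test, and repeated measures for viral load are named only for continuous values. Nor would a repeated-measures model carry the power over to the 12-month contrast: the calculation needs a 20-point difference averaged over the visits, whereas the cited 40% vs 60% is a 12-month difference.

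A reader might also infer that the power was certainly computed for a time-averaged analysis. The article does not show this. It gives neither the number of visits nor the variance form, and the correlation closes a list of assumptions in a paragraph that also covers the repeated-measures depression calculation. The shortfall in Step 2 does not depend on where the figures came from.

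Finally, it is fair to say that suppression is secondary. That limits the consequence but does not make the figure right, since the article offers it as a reason for the sample size.

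**Conclusion.** The power statement is wrong as written for the test that the article assigns to 12-month suppression. Under the article's own attrition, control rate and type I error, power is about 54% against a stated >80%, and about 76% against a stated >90%. A true 20-point gain would be missed about 46% of the time (100 − 53.9), where the text implies less than 20%.

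These values assume 1:1 allocation, equal attrition and a two-sided test. Relaxing sidedness or attrition singly leaves both figures short, and relaxing both still leaves the 20-point figure short. The fault is a mismatch between the power basis and the named test; it is not shown to be an arithmetic slip. It does not touch the two primary outcomes or the validity of Fisher's test, and it should not be read as saying that all biological outcomes are underpowered: CD4 count is another, and no power is claimed for it.

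**What to change.** In Sample Size Considerations, restate the power for the planned 12-month Fisher test as about 54% for a 20-point and 76% for a 25-point difference. State the assumptions with it: 64 analysed per arm, 1:1 allocation, equal attrition, control rate 0.4, two-sided 5%. Remove the claim that 160 participants give >80% and >90% power for this outcome.

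If those two figures are kept, say that they apply only to a named repeated-measures analysis of binary suppression at 4, 8 and 12 months, and to the difference averaged over those visits. Give the number of visits and the variance form, since the 20-point figure sits at 79.6% to 80.7% with three. That route changes the quantity being estimated, so the text should say that the power does not apply to the 12-month contrast.

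Either change is a matter of wording and needs no new data. The cost is a less favourable stated power for a secondary outcome, and a 12-month null result that must be reported with its confidence interval rather than read as adequately powered.
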